## Methods/design

### Study design and procedure

This study protocol conforms to the Standard Protocol Items: Recommendations for Interventional Trials (SPIRIT) guidelines (see Additional file 1). This three-arm, single-blind, randomized controlled trial will investigate the treatment effects of AOT and MT versus a control intervention and accords with the SPIRIT Figure (Fig. 1). An estimated 90 patients with subacute stroke will be recruited to participate in this study. Each participant will receive 15 training sessions for 3 weeks. Licensed occupational therapists will be well trained in treatment protocols and study procedures to ensure the consistency of intervention delivery. The therapists were not blinded to the group assignment, given the nature of the intervention. In addition, all outcome measures will be administered to the patients by the same rater, who will be blinded to the subject’s group. Three evaluation time points will be used: baseline, immediately after 3 weeks of treatment, and 3 months after treatment. Prior to administration of outcome measures, a blinded rater will be trained on how to appropriately administer these assessments. Rater competence will be evaluated before proceeding to the trial.

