### Patient inclusion and exclusion criteria

The inclusion criteria of the participants will be: (1) diagnosed as having a unilateral stroke, (2) 1 to 6 months after stroke onset, (3) from 20 to 80 years of age, (4) a baseline score of the Fugl-Meyer Assessment (FMA) of 20 to 60 [28], (5) able to follow the study instructions (measured by the Taiwan version of the Montreal Cognitive Assessment) [29], and (6) capable of participating in therapy and assessment sessions. The exclusion criteria will be: (1) global or receptive aphasia, (2) severe neglect, and (3) major medical problems or comorbidities that influenced UE usage or cause severe pain.

In addition, if patients have no metal implants, no head traumas or neurosurgical operations, and can perform MEG motor tasks, they can additionally participate in the MEG assessment. For the MEG portion of the study, we expect to recruit 12 to 15 patients in each group. Patients can still participate in the study, receiving rehabilitation therapy and clinical evaluations, even if they do not meet the MEG eligibility criteria, or are not willing to participate in the MEG study. All participants must provide written informed consent before entering the study.

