### Randomization

The participants will be randomly allocated to one of the three treatment groups in a 1:1:1 ratio after baseline evaluation. The participants will be pre-stratified on the basis of the severity of UE motor deficits (FMA score: 20 to 40 (moderate-to-severe) versus 40 to 60 (mild-to-moderate) [28]) and side of lesion (right versus left) to assure baseline equivalence between the groups. The random assignments will be performed online using a web-based randomization tool (freely available at https://www.randomizer.org/). A research assistant who will not be involved in outcomes assessment or screening of subjects will independently manage the randomization procedure according to allocation concealment.

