### Data analysis

An intention-to-treat analysis will be performed. Two-way repeated measures analysis of variance (ANOVA) will be used to evaluate the treatment effects among the three treatment groups at the three assessments from different time points. The between-subject factor will be the group and the within-subject factor will be the time. The treatment efficacy will also be examined by determining the number of participants whose change score reaches the minimal clinically important difference (MCID) in the clinical outcomes, by using a chi-square test. The MCID values will be adopted either for the established values of outcomes or 10% of the total scores when it has not been established. A *p* value < 0.05 will be considered as indicating statistical significance.

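### Baseline FMA is analysed as an outcome level and the stratification factors are left out of the model: a modest loss of efficiency against the interaction test, a large one if the group main effect is used

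*Protocol article*

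**What the plan says.** The protocol article, Data analysis, names both the method and its terms: "Two-way repeated measures analysis of variance (ANOVA) will be used to evaluate the treatment effects among the three treatment groups at the three assessments", and then "The between-subject factor will be the group and the within-subject factor will be the time". No covariate or further factor is named, and the section does not say whether the group main effect or the group-by-time interaction is the test of treatment.

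Study design and procedure lists the visits: "Three evaluation time points will be used: baseline, immediately after 3 weeks of treatment, and 3 months after treatment". Under Randomization, participants are "randomly allocated to one of the three treatment groups in a 1:1:1 ratio after baseline evaluation". The first level of the time factor is therefore a value measured before any treatment was assigned.

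Randomization also says that participants are "pre-stratified on the basis of the severity of UE motor deficits" ("FMA score: 20 to 40 (moderate-to-severe) versus 40 to 60 (mild-to-moderate") and on "side of lesion (right versus left) to assure baseline equivalence between the groups". Neither factor appears in the stated model.

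**The concern.** No treatment effect can exist at a visit that precedes allocation. Putting that visit inside the within-subject factor has two consequences. The group main effect averages over it and is diluted. The interaction stays a proper test of treatment, but it spends 4 degrees of freedom on any departure from parallel profiles, and it uses baseline much as a change score does instead of regressing on it.

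Leaving out the strata matters because allocation forces the arms to be alike on baseline severity. If the model does not know this, its residual variance still counts variation that the design has removed from the group comparison. A test on which baseline severity weighs heavily then rejects too rarely.

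At stake is precision in a trial of 30 per group. The protocol already collects what is needed to recover it.

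**Working it through.** **Plan's own figure.** A plain three-group comparison at f = 0.30, power 0.80 and two-sided 0.05 needs 37 per group, close to the 36 at the top of the stated range. At the planned 30 it has power 0.71. The sample size section mentions no baseline correlation.

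**Inputs from the protocol article.** n = 30 per group, N = 90; alpha 0.05; d = 0.60 to 0.95 (Sample size calculation).

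**Assumptions, not in the documents.** Both active arms gain d over control. The correlations (baseline–post, baseline–3 months, post–3 months) are (0.6, 0.5, 0.7), (0.7, 0.6, 0.8) and (0.8, 0.7, 0.85). They are labelled below by the first value, r.

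**1. Effect size.** Means (0, 0.6, 0.6) have average 0.4, so f² = (0.16 + 0.04 + 0.04)/3 = 0.08 and N f² = 7.2.

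**2. Baseline-adjusted comparison at post-treatment.** Noncentrality is 7.2/(1 − r²) = 11.25 / 14.12 / 20.00 on 2 and 86 df. Power is 0.85 / 0.92 / 0.98.

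**3. Group main effect.** Averaging over three visits shrinks the effect to 2/3. The variance of the mean is (3 + 2 × sum of the correlations)/9 = 0.733 / 0.800 / 0.856. Noncentrality is 7.2 × (4/9)/variance = 4.36 / 4.00 / 3.74 on 2 and 87 df. Simulated power is 0.45 / 0.39 / 0.37, before any effect of stratified allocation.

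**4. Group-by-time interaction (4 df).** Simulated power is 0.76 / 0.86 / 0.96.

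| Scenario | r | Interaction | Adjusted, post-treatment | Difference (points) |
|---|---|---|---|---|
| d = 0.60, both follow-ups | 0.6 | 0.76 | 0.85 | +9 |
| | 0.7 | 0.86 | 0.92 | +6 |
| | 0.8 | 0.96 | 0.98 | +2 |
| d = 0.60, post-treatment only | 0.6 | 0.82 | 0.85 | +3 |
| | 0.7 | 0.94 | 0.93 | −1 |
| | 0.8 | 0.99 | 0.98 | −1 |

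At d = 0.95, sustained, both tests are above 0.99 and there is nothing to gain.

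**5. Where the gain comes from.** The adjusted variance relative to a change score is (1 − r²)/[2(1 − r)] = (1 + r)/2 = 0.80 / 0.85 / 0.90. The saving of 20%, 15% or 10% shrinks as r rises.

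**6. Effect of omitting the strata.** These simulations stratify allocation on baseline severity and side, with a common correlation of 0.7.
- No effect: the main effect without strata rejects about 0.2% of the time (1% or less over the settings tried). With strata it rejects 4.9%. The interaction rejects 4.2% (3.4 to 4.6% in further runs).
- f = 0.20: adding strata raises main-effect power from 0.10 to 0.41.
- f = 0.20, with continuous baseline FMA in the model: power at post-treatment is 0.632 without strata and 0.630 with them.

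**The case against.** The strongest reply is that nothing here is wrong in the sense of biased. The group-by-time interaction is a customary and valid test, its type I error is close to nominal, and an analysis plan that is not shown might add covariates. The first part stands: this is a point about efficiency. The last part helps little, because the article does not leave the model open. It names the method and both factors.

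Several stronger readings are tempting and should be resisted.

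- *The planned analysis leaves the trial badly underpowered.* A reader could reach interaction power near 0.47 by assuming a 5-point gain with SD 11.5 and r = 0.6. That is d = 5/11.5 = 0.43, below the protocol's 0.60 to 0.95, and neither figure is in the documents.
- *Baseline adjustment always wins.* It does not. If the effect is transient and the correlation high, the single-visit adjusted test is slightly weaker than the interaction. Larger gains, such as 0.74 against 0.95 at f = 0.30 and a common correlation of 0.5, come from averaging both follow-ups. That is a different test from a comparison at one visit.
- *The main-effect figures describe the planned test.* They apply only if the main effect is read as the treatment test. The article does not say that it is.
- *Omitting the strata spoils every standard error.* The severe conservatism belongs to the main effect; for the interaction it is mild. Once continuous baseline FMA is included, the strata change power by less than 1 point.
- *Time since stroke must be in the model.* Eligibility spans "1 to 6 months after stroke onset", but this is not a stratification factor and no figure in the documents shows what adjusting for it would gain.

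**Conclusion.** The point holds as a loss of efficiency. The stated model treats a pre-randomisation measurement as outcome and omits the factors that governed allocation.

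Against the interaction test, the loss is about 2 to 9 points of power at the protocol's lower effect size when the effect is sustained. It is nil at the upper effect size, and nil or a few points the other way when the effect has gone by 3 months. Against the group main effect the loss is large: about 0.4 power where a baseline-adjusted test has 0.85 or more, with rejection under the null of roughly 0.2 to 1% when allocation is stratified and the strata are ignored. Because the article does not say which of the two tests counts, the second case cannot be excluded.

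The sizes rest on assumed correlations, normal outcomes, 30 evaluable patients per group and equal effects in the two active arms. The direction against the main effect does not depend on the exact correlation within the range tried. The direction against the interaction does depend on whether the effect lasts. The change is worth making because it is nearly free, but the trial's validity does not hang on it.

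**What to change.** Take post-treatment and 3-month FMA as the responses. Include continuous baseline FMA as a covariate, the randomisation strata (severity band as used at allocation, lesion side) as factors, and group, visit and group-by-visit. Test the adjusted group difference at post-treatment for the immediate effect and at 3 months for retention; these are the two aims given under Objectives. State that the ANOVA group main effect is not the test of treatment.

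Nearly all the precision comes from baseline FMA; the strata go in so that the analysis matches the design. Time since stroke may be added as an option.

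The cost is a change of wording and three residual degrees of freedom (baseline, severity band, side). All these variables are already collected for eligibility or allocation. The one statistical price is slightly less power than the interaction test when the effect is transient and the correlation high. Trial status reports recruitment as ongoing at submission, so the wording should be settled before any analysis by arm.

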#### Primary outcomes

The upper-limb subscale of the FMA will be used to evaluate motor impairments [28]. The 33 items assess movements, reflexes, and coordination of the shoulder, elbow, forearm, wrist, and hand. The total score ranges from 0 to 66, with a higher score indicating less motor deficit. The psychometric properties of the FMA have been well established in patients with stroke [31].

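### Randomisation is stratified by FMA band and lesion side but the ANOVA leaves both out: with balanced strata, main-effect and single-visit tests are very conservative, while group-by-time is little affected unless band predicts gain

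*Protocol article*

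**What the plan says.** The Randomization section has patients "randomly allocated to one of the three treatment groups in a 1:1:1 ratio after baseline evaluation". Two pre-stratification factors are named. The first is "severity of UE motor deficits (FMA score: 20 to 40 (moderate-to-severe) versus 40 to 60 (mild-to-moderate"; the second is "side of lesion (right versus left) to assure baseline equivalence between the groups". On mechanics it says only that "The random assignments will be performed online using a web-based randomization tool"; no block size or other balancing method within strata is given.

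The first factor is the primary outcome itself, cut at baseline. Entry requires "a baseline score of the Fugl-Meyer Assessment (FMA) of 20 to 60", and of the outcome scale the Primary outcomes section says: "The total score ranges from 0 to 66, with a higher score indicating less motor deficit".

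The Data analysis section plans a two-way repeated measures ANOVA that "will be used to evaluate the treatment effects among the three treatment groups at the three assessments from different time points". It then fixes the factors: "The between-subject factor will be the group and the within-subject factor will be the time". No stratification factor or baseline covariate appears, and the section does not say whether the group main effect, the group-by-time interaction or a comparison at one visit is the test of treatment.

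**The concern.** When arms are balanced within strata, differences between strata drop out of the comparison of arm means. A model without the strata still counts those differences as error. Its standard error is then larger than the true sampling variation, so the test rejects too rarely. Here one stratum is a band of the outcome being analysed, so the excess can be large.

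At stake is a real effect being reported as no difference between groups. There is little power to spare: at 30 per group, a one-way three-group ANOVA has power of about 0.71 at f = 0.30, the low end of the effect range in the Sample size calculation section.

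**Working it through.** The article gives no error rate or SD that bears on this point, so there is no figure of its own to reproduce. Taken from the article: N = 90, three arms, three assessments including baseline, entry FMA 20 to 60, bands meeting at 40, maximum score 66, alpha 0.05. All distributions and SDs below are assumptions.

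**1. Share of baseline FMA variance carried by the band.** If scores are uniform on 20 to 60, the total variance is 40²/12 = 133.3. The band means are 30 and 50, so the between-band variance is 10² = 100. The share is 100/133.3 = 75%. For a normal with mean 40 and SD 10, truncated to 20 to 60, the share is about 68%.

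**2. Expected error rate without the strata.** Let R² be the share of the analysed variable's variance explained by the four strata. With near-perfect balance, the unadjusted F is about (1 − R²) times the adjusted F. The unadjusted critical value is F(2, 87) = 3.10. With 84 residual degrees of freedom after adding the strata (90 − 3 − 3), the true rejection rate is about P[F(2, 84) > 3.10/(1 − R²)]. For two numerator degrees of freedom, P(F > x) = (1 + 2x/84)^(−42).

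- Mean over the three visits, uniform baseline, simulated R² = 0.64: x = 8.61, rate about 0.04%.
- The same, truncated normal, R² = 0.53: x = 6.60, rate about 0.2%.
- Change score, R² = 0.17: x = 3.73, rate about 2.8%.
- Change score, R² = 0.33: x = 4.63, rate about 1.2%.

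**3. Simulation of the full 3 × 3 ANOVA.** Permuted blocks of 3 or 6 within strata; gain SD 3 to 10; measurement SD 3 to 5; lesion side unrelated to FMA; Greenhouse-Geisser correction for group-by-time; 5,000 runs per null scenario and 2,000 per alternative.

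| Test | Strata omitted | Strata included |
|---|---|---|
| Group main effect, null | 0.0–0.5% | 4.7–5.6% |
| Group-by-time, null, base case | 4.8–5.1% | 4.8–5.0% |
| Group-by-time, null, bands differ by 6 points in gain | 2.6–3.1% | 4.6–5.1% |
| Group-by-time, null, bands differ by 10 points in gain | 1.2% | 4.7% |
| Main effect, power, one arm +5 points | 3% | 39% |
| Group-by-time, power, one arm +5 points | 69% | 69% |

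With simple allocation the unadjusted main effect rejects at 4.9% under the null, and with unstratified allocation at 4.8%.

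**4. Comparison at a single visit.** Blocks of 3, gain of 10 to 30% of the distance to 66, gain SD 4, measurement SD 2. Under the null the test rejects at 0.0–1.2% without strata and 4.8–5.7% with them. With both therapies 4 points better, power is 9–50% without and 57–80% with.

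**5. Can band predict gain?** A patient entering at 60 can gain at most 66 − 60 = 6 points; one entering at 20 can gain 46. With a uniform baseline, the mean distance to the ceiling is 66 − 30 = 36 points in the lower band and 66 − 50 = 16 in the upper, a gap of 20. If patients gain 10, 20 or 30% of the remaining distance, the bands differ by 2, 4 or 6 points. A 10-point difference would need 50%.

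Under the assumptions of step 4, unadjusted group-by-time rejects at 4.4–4.9% for a 10% gain and 1.8–3.4% for 20 to 30%. For the baseline-to-post change at 20 to 30%, adding the strata moved power from 87% to 91% or from 79% to 88%. With a regression slope of later on baseline score of 0.8 or 0.7, it moved from 88.4% to 91.9% (3.5 points) or from 79.3% to 89.9% (10.6 points). For the full group-by-time test at 20 to 30%, power spanned 71–89% without strata and 87–91% with, so the least favourable scenario there lost at least 87 − 71 = 16 points.

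**The case against.** A reader might infer that the trial's test of treatment rejects far below 5%. The article does not support that. In a group-by-time design that includes baseline, treatment is ordinarily read from the interaction. Its error term is within-patient, so the stable level that the band mainly captures cancels. The main effect averages in a visit before any treatment, which makes it a poor treatment test with or without strata. This objection stands, and it limits the near-zero error rates to the main effect and to single-visit comparisons.

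Those rates also need effective balance within strata. The article aims at baseline equivalence but describes no blocking, and under simple allocation the rate is about 5%. That stands as a condition. Efficiency is still lost: under unstratified allocation with a 20% gain, adding strata raised power from 15% to 41% for the main effect and from 31% to 68% at the post-treatment visit.

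Single-visit tests are not explicitly planned. However, the analysis sentence refers to effects among groups at the assessments, and the Objectives section separates immediate from retention effects, so such comparisons are a natural reading.

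Nothing in the article shows that lesion side predicts FMA, and no gain from including it has been demonstrated. It belongs in the model because patients are randomised by it.

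Finally, covariates are often left to an analysis plan. But the article does more than stay silent: it states what the between-subject factor is.

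**Conclusion.** The point holds in a limited form: the stated model omits the factors by which patients are randomised and does not name the effect that tests treatment. If strata are balanced by allocation, a main-effect or single-visit test has a type I error of about 0 to 1% and loses much or most of its power. Group-by-time is close to nominal if band does not predict gain. If it does, as the ceiling makes plausible, the error rate falls to about 1 to 3% and omitting the strata costs roughly 3 to 10 percentage points of power, more in the least favourable scenario run. The lowest rate, 1.2%, needs a 10-point difference in gain between bands.

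The direction is conservative throughout, and no added false positives follow. All rates depend on assumed baseline distributions, SDs, gains and blocking, since the article gives none. The point concerns the ANOVA of continuous outcomes, not the chi-square test of MCID responders.

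**What to change.** - Name the treatment test: group-by-time, or a baseline-adjusted comparison between arms at a named visit. Adding strata to the main effect alone is not enough; its power for a 5-point benefit in one arm is still only 39%.
- Include the FMA band as recorded at randomisation (or the baseline FMA score) and lesion side, each with its interaction with time, in the model for the FMA and the other continuous outcomes.
- State how allocation is balanced within strata, so that the analysis can be seen to match it.

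Both factors are already recorded for randomisation. The cost is a sentence or two in the Data analysis and Randomization sections and a few degrees of freedom.

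### The MCID responder comparison uses an unadjusted chi-square test although randomisation is stratified by baseline FMA and lesion side; a stratified test costs almost nothing and gains power if baseline predicts response

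*Protocol article*

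**What the plan says.** Protocol article, Data analysis: the main comparison is a group-by-time repeated measures ANOVA. Efficacy is then also examined by "determining the number of participants whose change score reaches the minimal clinically important difference (MCID) in the clinical outcomes", and this is done "by using a chi-square test". The MCID is an established value or "10% of the total scores when it has not been established". No stratum or covariate is named for this comparison.

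Protocol article, Randomization: patients go to "one of the three treatment groups in a 1:1:1 ratio after baseline evaluation". They are "pre-stratified on the basis of the severity of UE motor deficits" (FMA 20 to 40 versus 40 to 60), and also on "side of lesion (right versus left) to assure baseline equivalence between the groups". That makes four strata.

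Protocol article, Patient inclusion and exclusion criteria: entry requires "a baseline score of the Fugl-Meyer Assessment (FMA) of 20 to 60". Under Primary outcomes, the upper-limb FMA runs from 0 to 66.

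**The concern.** The design treats baseline FMA and lesion side as important enough to balance on, yet the responder analysis pools over both. Whether a patient gains a fixed number of FMA points may well depend on where that patient started. If so, stratified allocation removes the baseline differences between arms, but the pooled chi-square test still counts baseline variation as noise. Its null variance is then too large. A true difference in response rates on the primary outcome measure would be missed more often than necessary, with only 30 patients per arm.

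**Working it through.** **The plan's own figure.** The plan states no response rate and no power for the responder comparison, so there is nothing to reproduce. The 30 per group in Sample size calculation comes from an effect size for a three-group comparison of means.

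**Inputs from the article.** Three arms of 30; 1:1:1 allocation; four strata; baseline FMA 20 to 60; scale maximum 66; *d* from 0.60 to 0.95; significance level 0.05.

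**Assumptions.** Baseline FMA is uniform on 20 to 60, and lesion side is split 50:50. Allocation is in blocks of three within strata; the article names no block scheme. The first model puts control log-odds of response at -0.6 at mean baseline, adds 1.5 in both active arms (odds ratio e^1.5 = 4.5), and lets log-odds fall with baseline at the slope shown.

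**Headroom.** It runs from 66 - 20 = 46 points to 66 - 60 = 6 points. If the 10% fallback applied to the FMA, the threshold would be 0.10 × 66 = 6.6, and a patient entering at 60 could not respond. The article does not say whether the fallback applies to the FMA.

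**Why pooling is conservative.** With stratum weights w_s, response rates p_s and overall rate p:

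p(1 - p) = Σ w_s p_s(1 - p_s) + Σ w_s (p_s - p)²

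The chi-square test uses the left side as its null variance. When arms are balanced within strata, the second term on the right does not contribute to differences between arms. The test's variance is therefore too large whenever the p_s differ, and correct when they do not.

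**Simulation 1: response depends on baseline through a logistic slope** (3,000 runs per setting; simulation standard error at most √(0.5 × 0.5/3000) = 0.009). The tests are the Pearson 3 × 2 chi-square, the generalised Cochran-Mantel-Haenszel (CMH) test over the four strata, and a likelihood-ratio test from logistic regression on group, baseline FMA and side.

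| Slope per SD | Type I: chi-square / CMH / logistic | Power: chi-square / CMH / logistic | CMH minus chi-square |
|---|---|---|---|
| 0 | 0.050 / 0.048 / 0.058 | 0.845 / 0.841 / 0.854 | -0.4 points |
| 0.5 | 0.047 / 0.049 / 0.061 | 0.814 / 0.823 / 0.839 | 0.9 points |
| 1.0 | 0.028 / 0.042 / 0.054 | 0.671 / 0.727 / 0.773 | 5.6 points |
| 1.5 | 0.017 / 0.040 / 0.059 | 0.483 / 0.629 / 0.692 | 14.6 points |

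Further runs of the same set-up put chi-square type I error at 0.045 for slope 0.5, between 0.03 and 0.04 for slope 1.0, and about 0.02 for slope 1.5. They put CMH power at 0.62 for slope 1.5, so the loss there is 14 to 15 points.

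**Simulation 2: FMA gains generated directly** (assumed mean control gain 5, SD 6, threshold 6.6, gain capped at the available headroom; active arms shifted by *d* × 6). Power is chi-square / CMH / logistic.

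| Model | *d* = 0.60 | *d* = 0.95 |
|---|---|---|
| Gain proportional to headroom | 0.33 / 0.39 / 0.44 | 0.67 / 0.73 / 0.78 |
| Gain unrelated to baseline, only the cap acts | 0.44 / 0.43 / 0.46 | 0.84 / 0.83 / 0.85 |

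The ceiling alone therefore costs the chi-square test practically nothing. The expected gain itself has to vary with baseline.

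**How strong the slopes are.** The SD of a uniform 20 to 60 score is 40/√12 = 11.5, so the entry range spans 40/11.5 = 3.46 SD (unrounded SD). Slopes of 0.5, 1.0 and 1.5 then mean that the odds of response differ between the two ends by factors of e^1.73 = 6, e^3.46 = 32 and e^5.20 = 180.

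**The case against.** The strongest reply is that the chi-square test is valid here and that the benefit of changing it is unknown. The documents give no response rate and no prognostic strength. The steepest slope is extreme, and at the moderate slope the gain is about one point, the same order as the simulation error. All of this stands, and it limits the point to a low-cost gain in efficiency.

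Several stronger readings are tempting, but the documents do not support them:

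- **That limited headroom by itself causes the loss.** The cap-only model shows that it does not.
- **That the test is conservative however patients are allocated.** With simple 30/30/30 allocation and no strata, simulated type I error of the chi-square test was 0.048 to 0.050. Conservatism needs balance within strata. The article plans stratification but names no blocks.
- **That the trial's planned power is affected.** The responder comparison is an additional analysis, and the sample size was not derived from it.
- **That the argument covers every outcome.** The responder test applies to the clinical outcomes in general, while the headroom reasoning concerns only the FMA.
- **That the plan will yield nothing but a p value.** The article says responder numbers will be determined and does not restrict reporting. Pairwise contrasts and intervals may properly sit in a statistical analysis plan that is not shown.

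An unseen analysis plan could also add an adjusted analysis. The article nevertheless names the unadjusted test, so this is a stated method that can be improved, not a missing detail.

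**Conclusion.** The point holds as a modest improvement to a supplementary analysis. The plan names an unadjusted test for responders although it randomises within strata. If response depends on baseline FMA and the arms are balanced within strata, the test falls below its nominal level and gives up about 1, 6 and 14 power points against CMH at the three slopes, or about 6 points when gain is proportional to headroom. If neither stratification factor predicts response, the two tests perform alike. Dependence on baseline is plausible given the wide entry range, but it is an assumption. The direction of the effect is secure, and its size is not.

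**What to change.** In Data analysis, replace the plain chi-square test of MCID responders by a generalised Cochran-Mantel-Haenszel test (2 degrees of freedom for three arms) over the FMA-band by lesion-side strata. Use the stratum recorded at allocation, because the two FMA bands as printed share the score 40. Preferably show each active arm versus control with a 95% CI.

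Logistic regression on group, baseline FMA and lesion side is an acceptable alternative with somewhat more power in these simulations. Part of that advantage is not real, because its type I error was 0.054 to 0.067 at 90 patients. It also gives a conditional odds ratio, which is a different quantity from a comparison of overall response proportions.

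The cost is a change of wording, as both factors are known before randomisation. When baseline did not matter or only the cap acted, CMH lost at most 0.9 power points (0.478 versus 0.469, cap-only model with a threshold of 5 points and *d* = 0.60).
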